## Abstract

**Background:**

Currently, conventional medicine for stroke treatment remains at a standstill. Korean medicine (KM), which is in high demand in Korea, has been shown to have a therapeutic effect on stroke; however, considering the absence of epidemiological and clinical characteristics of patients receiving KM for stroke in Korea and prospective, large-scale, long-term studies on the efficacy and safety of KM, the acquisition of data from KM treatments on stroke is essential.

**Objective:**

We aimed to collect and analyze data on the major clinical characteristics of patients with stroke receiving KM treatment and investigate the effectiveness and safety of KM in the Korean population.

**Methods:**

The Registry of Stroke in Korean Medicine Hospital (RoS-KoMH) is a prospective, multicenter, observational disease registry aimed at collecting data from 500 sets of patients at multiple timepoints. Eligible adult patients diagnosed with cerebral infarction, cerebral hemorrhage, or subarachnoid hemorrhage who visited 4 KM hospitals as outpatients or inpatients will be continuously registered using the electronic case report form. Baseline data at the first visit; KM treatment, rehabilitation therapy, and concomitant therapy during the visit; stroke evaluation every 4 weeks after the first visit; laboratory findings at discharge or the last visit; and safety evaluation information after each acupuncture or pharmacopuncture treatment will be collected.

**Results:**

The study was funded on August 19, 2020, by the Ministry of Health and Welfare, Republic of Korea, and recruitment for the study started on November 3, 2021. As of September 25, 2024, a total of 410 participants have been recruited.

**Conclusions:**

The RoS-KoMH study is the first and largest multicenter, prospective registry to record comprehensive data on KM treatment of stroke. The results of this study will provide high-quality evidence on the current state of stroke treatment using KM in actual clinical practice, as well as treatment effectiveness and safety, and will consequently contribute to the promotion and standardization of therapeutic interventions for stroke in Korea.

**Trial Registration:**

Clinical Research Information Service KCT0008494; https://cris.nih.go.kr/cris/search/detailSearch.do?seq=23999&search_page=L&search_lang=&class_yn=

**International Registered Report Identifier (IRRID):**

DERR1-10.2196/67850

## Introduction

Stroke is the second leading cause of death worldwide and is characterized by high mortality, morbidity, disability, and recurrence [1]. Although the mortality rate is decreasing owing to advances in risk factor control, treatment techniques (eg, thrombolysis), and secondary prevention, the incidence is gradually increasing owing to the rapidly aging population [2-4]. In addition, many survivors experience sequelae, and poststroke disability places a significant burden on patients, caregivers, and society [5].

Current treatments for stroke have made significant progress but still have distinct limitations. Thrombolysis is the recommended first-line treatment for acute ischemic stroke to improve long-term functional outcomes. However, access is limited by narrow time windows, high technical requirements, imaging dependence, and high costs [6]. Antiplatelets are recommended for most patients for the secondary prevention of ischemic stroke [7], but they have a recurrence rate of approximately 10%, have remained flat for decades [8], and carry a high risk of adverse effects, including a bleeding tendency [9]. For cerebral hemorrhage, there are no special treatment options other than blood pressure management unless surgery is indicated [10].

Korean medicine (KM), which includes acupuncture and herbal medicine, is a traditional medicine that falls under the category of traditional East Asian medicine and has a long history in Korea. More than 70% of Koreans experience KM treatment and report high treatment satisfaction [11]. As evidence accumulated on the effectiveness of KM treatment for stroke, the Korean Medicine Clinical Practice Guideline for Stroke was developed in 2021, recommending the use of KM treatments, such as acupuncture and herbal medicine, to improve symptoms, treat, and prevent stroke [12]. However, KM demand for stroke treatment is declining, with stroke as a reason for KM inpatient use decreasing from 20.4% in 2014 [13] to 3.3% in 2022 [11]. This is because the epidemiological and clinical characteristics of patients receiving KM for stroke have not been investigated in Korea, and KM for stroke has been criticized for its low-quality evidence of efficacy and safety. Therefore, there is a need for a large-scale, prospective study on KM in patients with stroke.

A registry is a method for building a unified system by recording and sharing large-scale data in the health care field. Ongoing stroke registries in Korea include the multicenter prospective stroke registry (Clinical Research Collaboration for Stroke in Korea) [14] and a multicenter, prospective cohort study on stroke rehabilitation (Korean Stroke Cohort for Functioning and Rehabilitation) [15]. However, these were both registry studies on Western medicine, and no registry studies on stroke involving KM have been conducted in Korea. In China, a multicenter registry of traditional Chinese medicine for stroke has been organized and is currently enrolling patients [16]. In Taiwan, the characteristics of usage and outcomes of traditional Chinese medicine treatments, such as acupuncture and herbal medicine, for stroke have been analyzed using large-scale, national health insurance data [17,18]. Therefore, there is an urgent need for a stroke registry study of KM in Korea.

We present the rationale and design of the Registry of Stroke at Korean Medicine Hospital (RoS-KoMH). The RoS-KoMH aims to establish a multicenter, prospective registry of stroke in KM hospitals to explore the demographics, clinical presentation, treatment usage status, therapeutic outcomes, and safety of patients treated in KM hospitals and to collect clinical evidence to improve future treatment outcomes.

## Methods

### Study Design

The RoS-KoMH is a voluntary multicenter, prospective, observational disease registry attempting to explore the demographics, clinical features, treatment status, therapeutic outcomes, and safety of patients with stroke in Korea who are treated using KM in KM hospitals and establish clinical evidence to improve treatment outcomes in the future. A flowchart of the study process is shown in Figure 1. This study will be conducted by the Kyung Hee University Korean Medicine Hospital (KH) located in Seoul, Dongguk University Ilsan Korean Medicine Hospital (DG) located in Gyeonggi-do, Wonkwang University Gwangju Medical Center (WK) located in Gwangju, and Pusan National University Korean Medicine Hospital (PS) located in Gyeongsangnam-do. The protocol was registered with the Clinical Research Information Service (KCT0008494) on June 2, 2023, and reported in accordance with the SPIRIT (Standard Protocol Items: Recommendations for Interventional Trials) checklist (Multimedia Appendix 1).

**Figure 1 figure1:**
[figure not shown]
Flowchart of the study process. Stroke assessments at the initial assessment involve the manual muscle testing (MMT) grading system, modified Ashworth scale (MAS), grasp power, WIN-TRACK, timed up and go (TUG) test, modified Barthel index (MBI), fatigue assessment scale (FAS), fatigue severity scale (FSS), National Institutes of Health stroke scale (NHISS), Korean standard pattern identification (K-SPI) for stroke questionnaire, heart-kidney noninteraction questionnaire, Korean version of the mini-mental state examination (MMSE-K), and patient health questionnaire-9 (PHQ-9). Subsequent stroke assessments involve the MMT, MAS, grasp power, WIN-TRACK, TUG test, MBI, FAS, FSS, NHISS, K-SPI for stroke questionnaire, and heart-kidney noninteraction questionnaire. Korean medicine (KM) treatments include acupuncture, electroacupuncture, bee venom acupuncture, pharmacoacupuncture, indirect moxibustion, direct moxibustion, and cupping. HS, hemorrhagic stroke; IS, ischemic stroke; SAH, subarachnoid hemorrhage.

### Study Participants

#### Inclusion Criteria

The inclusion criteria for the study are as follows:

Men and women aged 19 years or older.Patients diagnosed with a stroke (including ischemic stroke, hemorrhagic stroke, or subarachnoid hemorrhage; 10th revision of the International Classification of Diseases codes I60-I63) based on the results of clinical examination and radiologic examination and receiving treatment at an outpatient clinic or an inpatient ward of a KM hospital.Patients who understood the purpose and intent of the study and voluntarily agreed to participate through written consent from the patient or their caregiver or representative.

#### Exclusion Criteria

The exclusion criteria for the study are as follows:

Patients with traumatic hemorrhagic stroke or traumatic subarachnoid hemorrhage.Patients who suffer from diseases that can affect acupuncture, electroacupuncture, pharmacopuncture, bee venom injection, moxibustion, or cupping (eg, clinically severe skin diseases and blood clotting disorders) and therefore cannot be treated.Patients judged by the investigator to be physically and mentally unsuitable for participation in the registration study based on examinations and laboratory findings.

#### Dropout Criteria

The following patients will be considered dropouts:

Patients discharged within 4 weeks of admission or lost to follow-up within 4 weeks of the first outpatient visit.Participants who are noncompliant with the investigator’s instructions.Participants who withdraw consent or request discontinuation.

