### Number of Participants

The purpose of this study was not to statistically verify the intervention effect of KM treatment for stroke but to explore the demographics, clinical aspects, treatment status, and therapeutic efficacy and safety of KM for patients with stroke patients in Korea and to provide clinical evidence to improve the therapeutic effect of KM treatment in the future.

Accordingly, a total of 500 sets of clinical information on patients with stroke will be collected based on the opinions of the researchers, considering the financial resources, the environment in which the study is conducted, and the appropriate number needed to achieve the goal. One set was defined as a stroke patient for whom information was collected at the time of the first outpatient visit or admission, and additional information was collected at any point (4, 8, or 12 weeks) after the first outpatient visit or admission. For example, if information was collected for a single patient once upon admission, once in the fourth week of hospitalization, and once again in the eighth week of hospitalization, 2 sets of information would be considered collected.

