Some characteristics of KM have made it difficult to build high-level evidence for it. In other words, KM is an empirical medicine that has accumulated over a long period, and it is difficult to standardize and objectively evaluate treatment because it provides customized treatment according to patient characteristics and requires a long treatment period and long-term follow-up. One way to supplement these points is to collect and use large-scale data [32]. Large-scale data use studies on KM in Korea are rare. In Taiwan, 99% of people are enrolled in national health insurance, and most traditional medicine treatments, including traditional Chinese medicine, are covered by national health insurance and used to generate evidence and improve treatment quality [33]. However, in the case of health insurance databases in Korea, KM is limited in that data cannot be obtained because major treatments such as herbal medicine (with some exceptions), pharmacopuncture, and bee venom acupuncture are not covered by national health insurance. Therefore, we designed the RoS-KoMH to compensate for these limitations by collecting information that can be obtained when treating patients with stroke patients at KM hospitals that actually treat stroke.

The RoS-KoMH protocol has some limitations. Although the RoS-KoMH registry collects longitudinal and multidimensional data, multivariate analyses, such as regression modeling or adjustment for potential confounders, have not yet been applied, which may limit causal inference regarding treatment outcomes given the variability in patient comorbidities and interventions. In addition, since the RoS-KoMH is a real-world, hospital-based, observational registry, it relies on voluntary participation to reflect the natural flow of patients receiving KM treatment for stroke in a routine clinical setting, which may lead to selection bias. The results of this study will provide evidence on the efficacy and safety of KM treatment for stroke to facilitate and standardize the optimization of individualized interventions for stroke prevention and treatment in Korea. Therefore, it is suggested that a registry study focusing on KM treatment be conducted using a stratified or consecutive sampling design as a follow-up to this study.

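### The dropout rule and the definition of a set make the registry's counted population conditional on about 4 weeks in care, at odds with its aim of describing routine practice

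*Protocol article*

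**What the plan says.** All references are to the Protocol article.

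- **Dropout Criteria.** The list opens with "The following patients will be considered dropouts". Its first entry is "Patients discharged within 4 weeks of admission or lost to follow-up within 4 weeks of the first outpatient visit". Its second is "Participants who are noncompliant with the investigator’s instructions", with no definition of the instructions meant. The third covers withdrawal of consent and requests to stop. The first two entries make no distinction by reason for leaving.
- **Number of Participants.** The size is fixed by judgement: "a total of 500 sets of clinical information on patients with stroke will be collected based on the opinions of the researchers". A set needs baseline information and that "additional information was collected at any point (4, 8, or 12 weeks) after the first outpatient visit or admission". One patient can supply several sets. The stated purpose is to "explore the demographics, clinical aspects, treatment status, and therapeutic efficacy and safety of KM for patients with stroke patients in Korea".
- **Table 2 and Follow-Up Measures.** Stroke assessments are made at baseline and every 4 weeks. At discharge or the final visit only laboratory findings are scheduled. Treatment use is recorded at each visit or inpatient day, and safety after each needle treatment, from the start.
- **Data Analysis.** Descriptive statistics, with change from baseline for repeated measures. The section neither limits the analysis to sets nor says how dropouts are handled.
- **Discussion.** The registry relies on voluntary participation "to reflect the natural flow of patients receiving KM treatment for stroke in a routine clinical setting", and this is the only source of selection bias named.

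**The concern.** Length of stay is a result of the patient's condition and care, not a baseline characteristic. In a descriptive registry, a rule that depends on it selects the population on something that happens after entry. Patients may leave before week 4 because they recovered, worsened, moved elsewhere or tolerated treatment poorly. They may differ from those who stay in severity, treatment pattern and adverse events.

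Noncompliance is a similar case. The registry assigns no treatment, so in routine care noncompliance is something to describe rather than a natural reason for setting a participant aside.

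At stake is what the final tables represent. If they cover only patients who stayed about 4 weeks and were compliant, they do not describe the patients who come to these hospitals with stroke, and a reader of the stated limitations would not know it.

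**Working it through.** **1. The plan's own figures.** The target of 500 has no alpha, power, effect size or dropout rate behind it, so there is no formula to reproduce. The site counts in Results add up: 171 + 88 + 125 + 26 = 410 sets.

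**2. What a set implies.** Up to three sets per patient are possible (weeks 4, 8 and 12). So 500 sets come from between 500/3, rounded up to 167, and 500 patients. Each of them has a record at week 4 or later.

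**3. A patient who leaves on day 20.** Reading the sections together:

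| Element | Status for this patient |
|---|---|
| Dropout Criteria | Dropout (discharged or lost before 4 weeks) |
| Set | None: no record at 4, 8 or 12 weeks |
| Change in stroke assessments | None: first repeat is at week 4, none at discharge |
| Change in laboratory findings | Possible: scheduled at baseline and at discharge or last visit |
| Baseline, treatment and safety data | Scheduled up to the day of leaving |
| Place in the analysis | Not stated |

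The first three rows are fixed by the text. The conditioning on about 4 weeks thus holds for the counted population and for change in the stroke assessments. It would reach the laboratory, baseline, treatment and safety tables only if dropouts, or patients without a set, were left out of them.

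**4. How many patients could lie outside the sets.** The share d leaving before week 4 is not given; 10% to 40% is assumed. With n patients who form sets, enrolment is n/(1 − d), rounded up.

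| d | One set each (n = 500): enrolled, outside | Three sets each (n = 167): enrolled, outside |
|---|---|---|
| 10% | 556, 56 | 186, 19 |
| 20% | 625, 125 | 209, 42 |
| 30% | 715, 215 | 239, 72 |
| 40% | 834, 334 | 279, 112 |

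**5. Effect on a safety proportion, if early leavers were left out.** The all-patient proportion is (1 − d) × p(stay) + d × p(leave). All risks are assumed: 5% in stayers, and 5%, 10% or 15% in leavers. The reported figure would be 5.0% in every cell.

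| d | leavers 5% | leavers 10% | leavers 15% |
|---|---|---|---|
| 10% | 5.0% | 5.5% | 6.0% |
| 20% | 5.0% | 6.0% | 7.0% |
| 30% | 5.0% | 6.5% | 8.0% |
| 40% | 5.0% | 7.0% | 9.0% |

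Example: 0.8 × 5% + 0.2 × 15% = 7%, and 1 − 5/7 = 29% understatement. At equal risk the proportion is unbiased, although the share d of patients with events would still be missing from the count. If leavers have lower risk, for instance because they receive fewer treatments, the reported proportion would be too high instead.

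**The case against.** A reader might infer that the registry loses early deaths, transfers, recoveries and adverse events. The text does not support that as a fact. It calls these patients dropouts, but nowhere says that their records are deleted or omitted from any description. Safety and treatment data are scheduled from the first day. The rule does not mention death or transfer.

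A reader might also infer that the registry cannot show why patients leave. The case report form is not shown, and Table 1 is a condensed list. It includes haemorrhage affecting vital signs and other adverse effects, and treatment end dates are recorded. A missing field for reason of leaving cannot be established from the article.

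Three further arguments have weight:

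- The set is a counting unit for the target, not a declared analysis population, and analysis sets may be defined in a full protocol or analysis plan.
- A patient who leaves before the first 4-weekly assessment has no change in those scales under any wording.
- The instructions in the noncompliance entry may concern study procedures, and for outpatients the 4-week entry covers only loss to follow-up, an ordinary meaning of dropout.

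These arguments remove any claim of certain loss and any fixed size of bias. They do not remove the stated rule. Ordinary discharge before 4 weeks counts as dropout, the target counts only those who stayed, and the limitations do not mention it.

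**Conclusion.** The point stands in a limited, partly conditional form.

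- **Fixed by the text:** the counted population and the change results for stroke assessments are conditional on remaining about 4 weeks. This conflicts with the descriptive aim and is not acknowledged as a source of selection.
- **Conditional:** if the analysis follows the dropout rule or the sets, early leavers and noncompliant participants also drop out of the baseline, treatment and safety denominators.
- **Size:** not computable, because the documents give no rates of early leaving, noncompliance or adverse events. Under the assumed ranges, a reported 5% would stand against a true 5% to 9%. Both the exclusion and the difference in risk are assumptions.

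It is worth correcting, but does not invalidate the registry. Results states that no analysis has been done and that recruitment runs to December 31, 2026, so the correction can still be made in advance.

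**What to change.** 1. State that early discharge, early loss and noncompliance are not grounds for removal from analysis.
2. Include all consented patients, subject to withdrawal of consent, in the baseline, treatment and safety descriptions.
3. Restrict only the change-from-baseline tables to patients with the relevant follow-up value, and give the number in each.
4. Report the number and baseline profile of patients without a 4-week assessment beside those with one.
5. Add the conditioning on a stay of about 4 weeks to the limitations.
6. Where the hospital record allows, tabulate the date and reason for leaving.

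Items 1 to 5 need wording and use data already scheduled, with some extra data cleaning for early leavers. Item 6 costs more: some chart review for patients already registered, and possibly a minor amendment of the case report form at four sites, each of which has its own ethics approval. If a full protocol or analysis plan already keeps these patients in the analysis, one sentence in the article saying so would cover items 1 and 2. Items 4 and 5 would still be needed.

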### Number of Participants

The purpose of this study was not to statistically verify the intervention effect of KM treatment for stroke but to explore the demographics, clinical aspects, treatment status, and therapeutic efficacy and safety of KM for patients with stroke patients in Korea and to provide clinical evidence to improve the therapeutic effect of KM treatment in the future.

Accordingly, a total of 500 sets of clinical information on patients with stroke will be collected based on the opinions of the researchers, considering the financial resources, the environment in which the study is conducted, and the appropriate number needed to achieve the goal. One set was defined as a stroke patient for whom information was collected at the time of the first outpatient visit or admission, and additional information was collected at any point (4, 8, or 12 weeks) after the first outpatient visit or admission. For example, if information was collected for a single patient once upon admission, once in the fourth week of hospitalization, and once again in the eighth week of hospitalization, 2 sets of information would be considered collected.

### Recruitment of Participants

The participants of the study will be patients with stroke who visited as outpatients or were admitted as inpatients to KM hospitals. Patients who are deemed suitable for participation in the study based on the inclusion and exclusion criteria will be recruited by obtaining voluntary written consent from the participants or their caregivers within 7 days of their outpatient visit or hospitalization at a KM hospital after the research staff have provided all information related to the study. All information obtained from patients was collected and recorded using an electronic safety case report form (eCRF) that was developed and validated by the principal investigators and research staff from all institutions participating in the study (KH, DG, WK and PS) over a period of approximately 10 months through multiple face-to-face and web-based meetings, and all assessment tools included in the eCRF were developed, validated, and used in clinical practice.

